In addition, other types of training such as physical activity of different kinds are also explored as a way to improve the physical and cognitive status. The term “physical activity” includes a large number of activities related to voluntary body movements [32]. A large body of evidence supports the beneficial effects of physical activity on executive functions and memory [56–61]. Although early physical activity intervention studies, which mainly centered on cardiovascular training, showed that cardiovascular activity produced increases in hippocampal volume in older adults while improving spatial memory performance [62, 63], other types of physical exercise, such as motor fitness and coordination training, also resulted in increased hippocampal volume in healthy older adults [60]. Complex physical activities such as dancing [64–66] or the practice of martial arts [67–71] have also shown beneficial effects on cognition in older adults.

Several studies suggest that social engagement plays a key role in the maintenance of cognitive functioning and psychological well-being in older adults [32, 72, 73] (for a recent review, see [74]). In the present multidomain intervention, social engagement is not considered a source of variance, as it is not a factor manipulated in the intervention, but, rather, a design feature included to enhance cognitive and physical functioning. So, cognitive and physical training, as well as their control activities, will be performed in a social environment. In this way, the four groups will be trained in the same social conditions; that is, in small groups and in the presence of a trainer.

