### Study design

Participants will complete one of the four combinations of cognitive training with video games and physical exercise. The cognitive component will be either a brain-training video-game program selected from Lumosity (cognitive intervention, CI) or video games not specifically designed to train particular cognitive functions such as attention, memory, or executive control (cognitive control, CC). The physical exercise component will be either a senior-friendly adaption of BODYATTACK™ (https://www.lesmills.com/), a combination of dance, aerobic, strength, and muscular resistance (exercise intervention, EI), or its control condition comprising stretching, toning, and relaxation (exercise control, EC). The duration of sessions for all groups will be the same, and all participants will perform physical exercise and video-gaming activities in a social environment (in small groups formed by 10–12 participants) and in the presence of the trainer.

To summarize, the study will have a 4 × 3 mixed factorial design with four intervention conditions—multidomain (CI + EI), uni-domain cognitive intervention (CI + EC), uni-domain physical intervention (EI + CC), and active control (CC + EC)—assessed at three different time points (pretest, posttest, 3-month follow-up), with “Type of training” as between-subject factors and “Time” as the within-subject factor. The dependent variables will be behavioral and/or electrophysiological measures of executive functions (inhibition, shifting, working memory), memory functions (short term and long-term visual and word memory), and emotional well-being, quality of life, and motivation.

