### Trial setting

This study will be conducted in Madrid (Spain) at the UNED Psychology building. The screening, pretest, posttest, and follow-up assessments will be conducted in our laboratories at the Psychology building. The training sessions of the four groups will be conducted in three waves in spaces specifically equipped and prepared for this purpose at our university site as well as at a city council facility.

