### Randomization and blinding

After the baseline assessments, participants will be randomly allocated to one of the four training protocols in a stratified process using the online tool Random Lists (move this to the other linehttps://www.randomlists.com/). [name] will generate the random sequence and will assign participants to interventions. At first, participants who came in couples will be randomly allocated as a unit to one of the four groups, and afterward the same procedure will be performed with the individual participants. This procedure aims to minimize dropouts due to separating couples in different groups. Participants and exercise instructors will be blinded to treatment allocation (single-blind). Data analysis will not be blinded, as it will be performed by the investigators who actively collaborate in the study. We do not envision any reason why participants should be unblinded, either during the trial or at the end of the study.

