### Statistical analysis

All data from participants with complete baseline assessment and who attended at least one training session will enter into a primary intention-to-treat analysis. For the secondary per-protocol analysis, only the data of participants with a complete cognitive assessment and an attendance rate ≥ 70% will be considered.

Executive functions (set shifting, maintenance, inhibitory control) and memory functions (short-term, visual, and verbal immediate and delayed memory) will be assessed at pretest, posttest, and follow-up. The statistical analysis corresponding to the behavioral results will be carried out with the SPSS statistical package for Windows (SPSS 25.0; IBM Corporation). Results will be considered significant at *p* < 0.05, with Bonferroni-corrected post hoc tests performed as appropriate. We will explore the missing data to ascertain their pattern and will apply an adequate technique of multiple imputation. Repeated ANOVA measures will be conducted with four groups (multidomain training, cognitive training, exercise training, active control) at three time points (pretest, posttest, follow-up) to test the primary hypothesis (i.e., differences in efficacy between interventions compared to the active control condition). Repeated ANOVA measures will also be performed to determine the effect of the interventions on secondary outcomes. To evaluate the effect size of the combined multimodal group versus each individual intervention group and the control arm, we will use multimodal regression with an interaction term. Electrophysiological data will be analyzed with CURRY 8.0.2, the EEGLAB toolbox [92], and the ERPLAB plugin for EEGLAB [98].

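### Couples are allocated as a unit and all arms train in small groups, but the named primary ANOVA and the sample size treat participants as independent

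*Protocol article*

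**What the plan says.** **Allocation** (Randomization and blinding): "participants who came in couples will be randomly allocated as a unit to one of the four groups"; single participants are allocated afterwards by the same procedure. The number of couples is not given.

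**Delivery** (Study design; Trial setting): all participants train "in small groups formed by 10–12 participants" with a trainer present, and "The training sessions of the four groups will be conducted in three waves", at the university and a city council facility.

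**Social setting** (Background): "social engagement is not considered a source of variance, as it is not a factor manipulated in the intervention". The same sentence says that the setting was included because it is meant to help functioning.

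**Analysis** (Statistical analysis): "Repeated ANOVA measures will be conducted with four groups (multidomain training, cognitive training, exercise training, active control) at three time points". For the size of the effects, "we will use multimodal regression with an interaction term". Neither model names couple, training group or wave. On multiplicity: "Results will be considered significant at *p* < 0.05, with Bonferroni-corrected post hoc tests performed as appropriate".

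**Sample size** (Sample size): an ordinary F-test with four groups, alpha 0.05, power 0.80 and f = 0.38, giving 124. This is raised to 144 (36 per arm) for 12% dropout, with no allowance for clustering.

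**The concern.** For participants who join as a couple, the randomised unit is the pair. For everyone, the treatment is received in company. A setting that is expected to help functioning, and that is delivered in a dozen or so separate groups, can work better in some groups than in others. Giving all arms the same kind of setting protects against bias between arms, but it does not remove correlation within groups.

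The planned ANOVA estimates its error from differences between individuals within an arm. If members of a group or couple change together, the variance of an arm mean is larger than that error term implies. P-values are then too small and intervals too narrow. Bonferroni correction does not repair this, because each p-value is too small before it is multiplied. With few groups per arm, a single group that does unusually well can pass for an effect of the intervention. The article's main question, whether the multidomain arm outperforms the single-domain arms and these outperform control, rests on exactly these contrasts.

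**Working it through.** **Inputs from the article.** 144 participants, 36 per arm; groups of 10–12; three waves; alpha 0.05; f = 0.38; power 0.80; dropout 12%; primary cognitive metrics defined as change from baseline.

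**Inputs assumed.** 36 / 12 = 3 training groups per arm, 12 in all. This fits three waves but is an inference. Training-group ICC of change: 0 to 0.10. Share q of participants in couples: 0.1 to 0.6. Partner correlation r: 0.1 to 0.4.

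**The plan's own figure.** A one-way F-test with four groups, f = 0.38, alpha 0.05 and power 0.80 needs N = 80 (power 0.803). At N = 124 the power is 0.952. So 124 is not reproduced from its stated inputs. That is a separate matter, but it bears on power below.

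**Training groups, m = 12.** Design effect DE = 1 + (m − 1) × ICC = 1 + 11 × ICC. The true standard error is √DE times the naive one, and the effective size is 144 / DE. Type I error comes from simulation under the null (4 arms × 3 groups × 12, at least 20,000 runs per setting), analysing change scores as if participants were independent. The familywise column covers all six pairwise comparisons, Bonferroni-corrected.

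| ICC | DE | SE ratio | Effective N | Omnibus error | Familywise error |
|---|---|---|---|---|---|
| 0 | 1.00 | 1.00 | 144 | 5% | 4% |
| 0.01 | 1.11 | 1.05 | 130 | 7% | 6% |
| 0.02 | 1.22 | 1.10 | 118 | 9% | 8% |
| 0.05 | 1.55 | 1.24 | 93 | 17% | 15% |
| 0.10 | 2.10 | 1.45 | 69 | 30% | 26% |

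Each corrected comparison has a nominal level of 0.05 / 6 = 0.83%. Its actual level is about 1.8 / 3.4 / 7.1% at ICC 0.02 / 0.05 / 0.10. With groups of 10, DE = 1 + 9 × ICC, which is 1.09 / 1.18 / 1.45 / 1.90 for ICC 0.01 / 0.02 / 0.05 / 0.10.

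**Couples alone.** DE = 1 + q × r. The smallest value is 1 + 0.1 × 0.1 = 1.01 and the largest 1 + 0.6 × 0.4 = 1.24. The actual level of a nominal 5% contrast is 2 × (1 − Φ(1.96 / √DE)), which is 5.1% at DE 1.01, 7.1% at 1.18 and 7.8% at 1.24.

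**Why the form of the model matters.** If baseline stays in the model as an outcome, a group effect that is constant over time cancels from the arm-by-time contrast. Simulating group effects that arise only after training, and fitting only such an intercept, leaves the arm-by-time error at about 9 / 17 / 31% for ICC 0.02 / 0.05 / 0.10. Testing arm against the variation between training groups on the change score, with 12 − 4 = 8 error degrees of freedom, brings the simulated error back to about 5% at every ICC above.

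**The case against.** - **No inflation need occur.** The article gives no ICC, and at zero the planned test is valid. Because the metric is change, stable traits that partners share largely cancel. Delivery is standardised: adaptive individual game accounts, predetermined game sequences and exercise sessions preset by the distributor. This stands, and it argues for the lower rows of ICC. It does not show zero, and at 0.01 the omnibus error is already about 7%.
- **Group structure is partly inferred.** A reader might take it that groups have fixed membership, or that each has its own instructor, slot and room, so that an instructor effect is confounded with arm. The article says none of this. It speaks of exercise instructors in the plural and of two sites, and the same instructors may lead several arms. The point does not need these claims; it needs only that people who train together may change together.
- **Unadjusted pairwise error is not the planned test.** Correct: post hoc tests are Bonferroni-corrected, so familywise error is the relevant figure. It is still inflated.
- **Power.** A reader might infer that the trial becomes underpowered. At the stated f = 0.38 the documents do not support that for moderate ICCs: with all 144 analysed, effective size stays above 80 up to an ICC of about 0.05.
- **Left to an analysis plan.** A condensed article may omit random-effect details. Here, however, the primary model is named, and as named it assumes independence.

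**Conclusion.** The point holds, as something that should be fixed. The named analysis and sample size assume independent participants, which the article's own allocation of couples and group delivery do not justify. The direction is certain for any positive correlation in change; the size is not, because neither the ICC nor the number of couples is given. Over assumed training-group ICCs of 0 to 0.10, with an inferred three groups of 12 per arm, omnibus error runs from about 5% to 30% and familywise error from about 4% to 26%. Couples add little on their own (DE about 1.01 to 1.24), but as randomised units they belong in the model. The harm is to type I error and interval width more than to power at the stated effect size.

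**What to change.** - Record a couple identifier and a training-group identifier for every participant.
- Replace the ANOVA by a linear mixed model of the post-test and follow-up outcomes adjusted for baseline, or of change from baseline. Fixed effects: arm, time, arm-by-time, wave and couple status. Random effects: participant, couple and training group.
- If baseline is kept as an outcome, use group-by-time and couple-by-time random effects instead of intercepts that are constant over time.
- Use Satterthwaite or Kenward-Roger degrees of freedom, and keep the cluster terms whether or not their variances look small.
- Report the ICCs, and state in the sample-size section what design effect the trial can bear.

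**Cost.** Two identifier variables and changed analysis wording; the planned statistical package can fit mixed models. The price is wider intervals and few degrees of freedom for arm contrasts. With 12 groups, four arms and three waves there are about 12 − 4 − 2 = 6 at group level when the group variance is not negligible. ICCs estimated from so few groups will be imprecise.

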### Participants

Participants will be male and female, healthy, and independently living volunteers aged between 60 and 80 years. Those who complete the baseline assessments and meet the inclusion criteria (see later) will be randomly assigned to one of the four intervention conditions. The timing of group allocation will take place between 1 and 8 weeks after baseline.

Participants may discontinue their intervention for personal or medical reasons. To minimize dropouts and improve adherence to the intervention, four face-to-face adherence reminder sessions will take place during the training program emphasizing the importance of training compliance. Furthermore, to increase participant retention and to reduce loss to follow-up, all participants will receive a personalized report of their performance and training progress at the end of the study. Participants will receive a small refund in compensation for their travelling expenses.

Even though this trial is low risk, participants might harm themselves during the practice of physical exercise. To minimize the risk of injuries, each participant will be carefully monitored during the training sessions. The interventions will be designed in collaboration with the exercise instructors, after a detailed analysis and taking into account each participant’s possible medical issues. Spontaneously reported adverse events or other unintended effects will be registered and analyzed, and if necessary the protocol will be modified to eliminate the causing element. We have signed an insurance policy in case any participant suffers harm during the physical training.

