### Interventions

Participants will complete 16 training sessions of sequentially combined physical and cognitive training, or the corresponding control activities. Participants will be trained in small groups on 2 days per week for 2 h. The first 60 min of each session will be dedicated to the exercise intervention (EI) or the exercise control activity (EC), followed by 60 min of cognitive training with video games (CI) or the cognitive control activity (CC). Both CI and CC will be conducted on tablets (Brigmton BTPC 1018OC). EI and EC will be led by physical exercise instructors and accompanied by a music soundtrack.

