#### Physical intervention

The exercise intervention will consist of BODYATTACK™, which is a registered trademark of moderate to high-intensity training that combines aerobic exercises with strength and balance exercises. During the exercise protocol, participants will train at 65–80% of their maximum heart rate. The training sessions are predetermined by the distributer and comprise standardized movements, exercises, and music soundtracks (see Table 2). Exercises include large plyometric movements and more controlled movements, and train equally upper and lower body muscles with dynamic movement coordination. The sequence of exercises is as follows: 10-min warm-up, 35-min main phase (with active recovery between intervals), and 10-min cool-down.

**Table 2 Tab2:** Description of the exercise intervention

Activity	Trained function	Description
Adaptation of “BODYATTACK™”	Cardiovascular fitness	Aerobic exercises
	Endurance	Strength moves
	Coordination	Movements to music soundtrack
	Balance	Stabilization exercises
	Flexibility	Stretching

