#### Electrophysiological measures

##### Electroencephalograph acquisition

While performing the experimental memory-based switching task, continuous electroencephalograph (EEG) activity will be recorded using a NuAmps amplifier (Neuroscan Inc.) inside a soundproof, electromagnetically shielded room. We will use a 34-channel elasticized Quik-Cap with Ag/AgCl sintered electrodes (American Medical EEG Association, 1991). To control ocular artifacts, vertical and horizontal electrooculograms will be recorded in two bipolar channels. Eye blinks and vertical eye movements will be monitored via electrodes located below and on the supraorbital ridge of the left eye. Horizontal artifacts will be monitored via electrodes on the outer canthus of each eye. Linked mastoids (A1, A2) will be used as a reference, and participants will be grounded to the AFz electrode. All data will be digitized using a NuAmps amplifier in continuous recording mode. The sampling rate will be 1000 Hz, and all channels will be online bandpass filtered (0.1–140 Hz) and notch filtered (50 Hz) to eliminate power line artifacts. Continuous data will be filtered offline using a digital Butterworth filter (0.1–40 Hz; 12 dB per octave roll-off), an infinite impulse response filter that achieves a given filtering characteristic. After filtering, data will be separated into baseline-corrected and nonoverlapping epochs time-locked to the target onset. Epochs containing high amplitude/frequency and muscle or other irregular artifacts will be removed by visual inspection. Only artifact-free epochs from correct trials will be selected for averaging. The existence of blinks and other ocular movements will not be a criterion for epoch rejection. This kind of artifact will be eliminated using Independent Component Analysis (ICA) [92–98]. After submitting EEG data to ICA decomposition, artifactual components will be removed by inspection of their activity, scalp topography, and spectral power. The length of the epoch in the target-locked ERP will be 1100 ms, and 600 ms in the response-locked ERP. We focus on P2, N2, and P2b. Analyses will be centered on the posttarget and postresponse ERPs at the midline electrodes located at the frontal, central, and parietal lobes (Fz, Cz, and Pz) where the components of interest are usually maximum. P2 is a positive ERP component associated with retrieval of stimulus–response sets that will be measured between 150 and 300 ms. N2 will be measured at the most negative pick between 150 and 400 ms after target onset. P3b will be measured in the time window of 300–600 ms after target onset. This wave is associated with context updating and working memory (see [75, 76, 87]).

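### Analysis is declared unblinded while EEG epochs and components are removed by inspection with nothing masking arm or visit, and instructors who lead the exercise arms are called blinded

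*Protocol article*

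**What the plan says.** Under Randomization and blinding, the protocol article says of the analysis: "Data analysis will not be blinded, as it will be performed by the investigators who actively collaborate in the study". No other reason is given. The same section names who is blinded: "Participants and exercise instructors will be blinded to treatment allocation (single-blind").

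Under Electroencephalograph acquisition, two steps depend on a person's judgement: "Epochs containing high amplitude/frequency and muscle or other irregular artifacts will be removed by visual inspection", and, after ICA decomposition, "artifactual components will be removed by inspection of their activity, scalp topography, and spectral power". No amplitude limit or other numeric rule is given for either. That section falls under the heading for primary outcomes; the secondary outcomes begin after it. Statistical analysis lists the EEG software (CURRY, EEGLAB, ERPLAB) alongside the behavioural analysis.

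Objectives and hypotheses expects shorter P2 latency and enhanced N2 and P3b in the multidomain arm than in either single-domain arm.

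On delivery, Interventions states: "EI and EC will be led by physical exercise instructors and accompanied by a music soundtrack". The Participants section adds: "The interventions will be designed in collaboration with the exercise instructors".

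**The concern.** Four things come together: analysts drawn from the active study team, a decision not to blind them, a cleaning step governed by judgement, and a hypothesis with a stated direction. Which epochs and components survive can alter the averaged waveform, and with it a peak or latency read inside a fixed window. If whoever makes those choices knows the arm or the visit, the choices can drift towards the expected result without any intent. That the analysts work on the trial is a reason to mask this step, not a reason to leave it open.

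The instructor statement is a separate matter. It tells readers that the people delivering the exercise are blind to allocation, when the design lets them see the exercise half of it. A reader judging performance bias would credit the trial with more protection than it can have.

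**Working it through.** **Unblinded analysis and EEG cleaning.** The plan has no figure of its own to reproduce, so the sections are compared first.

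- Randomization and blinding: analysis is not blinded.
- Statistical analysis: EEG processing is listed as part of the analysis, so the statement reasonably covers it.
- Electroencephalograph acquisition: epochs and ICA components are removed by inspection, without thresholds. N2 is then taken at the most negative peak between 150 and 400 ms, P2 between 150 and 300 ms, and P3b between 300 and 600 ms.
- Data monitoring committee and data management: forms carry coded IDs, and the lists linking IDs to identities are filed separately under lock. This is a confidentiality measure. It does not say that arm or visit is hidden from the person cleaning the EEG.

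No section masks arm or visit before cleaning and measurement are complete.

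**How much a shift would matter (illustration).** Inputs: alpha 0.05 (Statistical analysis); 124 required in total (Sample size), so 124/4 = 31 per arm; 36 per arm randomised. The bias *b*, in SD units, is an assumption. The true effect is set to zero.

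For two arms of *n*, SE = sqrt(2/*n*). With critical value *z*, the rejection rate is P(Z > *z* − *b*/SE) + P(Z < −*z* − *b*/SE).

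At *n* = 31, SE = sqrt(2/31) = 0.254. For *b* = 0.2, *b*/SE = 0.787, and with *z* = 1.960 the rate is P(Z > 1.173) + P(Z < −2.747) = 0.1205 + 0.0030 = 12.3%.

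For a Bonferroni correction over all six pairs of arms, alpha is 0.05/6 = 0.0083 and *z* = 2.638. Taking six pairs is also an assumption, because the plan does not fix the number of post hoc tests. For *b* = 0.2 the rate is P(Z > 1.851) + P(Z < −3.425) = 0.0321 + 0.0003 = 3.2%.

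| Assumed shift *b* | Uncorrected pair, 31 per arm | Uncorrected pair, 36 per arm | Bonferroni, six pairs, 31 per arm | Four-group F test, one arm shifted, 31 per arm |
|---|---|---|---|---|
| 0 | 5.0% | 5.0% | 0.8% | 5.0% |
| 0.1 SD | 6.8% | 7.1% | 1.4% | 6.4% |
| 0.2 SD | 12.3% | 13.6% | 3.2% | 10.9% |
| 0.3 SD | 21.9% | 24.7% | 7.3% | 19.4% |

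The F-test column uses a one-way noncentral F with 3 numerator degrees of freedom and effect size *f* = *b* × sqrt(3/16), as a simple stand-in for the planned repeated-measures ANOVA.

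**Instructor blinding.** The instructors lead EI and EC. EI is described thus: "The exercise intervention will consist of BODYATTACK™, which is a registered trademark of moderate to high-intensity training". EC is BODYBALANCE, built on Tai Chi, Yoga and Pilates. The two programmes are openly different, and the instructors help to design the interventions. Whoever leads a session therefore knows the exercise component. Two kinds of blinding remain possible: to whether the group goes on to CI or CC in the second hour, and to the study hypotheses. The sentence specifies neither.

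**The case against.** **The documents do not say that the EEG cleaner sees arm and visit.** This stands. Nothing identifies who cleans the data or what labels the files carry, and a condensed article may leave file handling to a fuller document. A reader might infer that investigators will knowingly delete data by arm; the text does not support that. It does declare unblinded analysis and counts EEG processing as analysis, so the plan as written permits unmasked cleaning.

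**No mechanism is shown that would push the results one way.** Partly stands. Removing artifacts before averaging need not favour the hypothesis, and no direction or size of bias can be established. The point is an open route to bias, not a demonstrated one.

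**The ERP measures are primary only by position.** Partly stands. They sit under the primary heading, but they belong to the second objective and lack the metric statement given for the behavioural measures. They are still hypothesis-bearing outcomes.

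**The error rates rest on an invented shift and the wrong test.** Stands as a limit. The shift is assumed, 31 per arm treats completers only whereas the plan is intention-to-treat with multiple imputation, and Bonferroni correction lowers the rates. They show sensitivity and are not an estimate for this trial.

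**Masking would not cure everything.** Stands. A reader might infer that it removes the bias. It does not reach delivery of the interventions or outcome testing, and it fails if an active investigator can recognise a participant from the code. Nor does the argument about visual judgement carry over to the computerised task-switching, N-back and Stroop data.

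**Allocation may mean the four-arm combination.** Possible. Instructors might then be blind to CI versus CC. That is one reading of an unclear sentence, and the sentence needs to say so.

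**Conclusion.** The concern holds in a limited form. The plan chooses unblinded analysis, cleans EEG data by judgement without numeric rules, and masks neither arm nor visit before P2, N2 and P3b are measured. That leaves an avoidable route to bias in the ERP results. Its size is unknown. The illustrative false-positive rate of about 7% to 22% depends on an assumed shift of 0.1 to 0.3 SD, 31 per arm and no multiplicity correction. With Bonferroni over six pairs, the per-contrast rate is about 1.4% to 7.3% against a nominal 0.8%. The behavioural outcomes are outside this finding.

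The instructor statement conflicts with the description of delivery. That conclusion needs no assumption: instructors who lead EI or EC cannot be blind to that component.

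Both parts are worth correcting and cheap to correct. Neither changes the sample size or alpha.

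**What to change.** 1. Recode the EEG files so that arm and visit are hidden from whoever carries out epoch rejection, component removal and component measurement. Use codes that the processor cannot trace to participants; the existing study IDs may not be enough for someone active in the trial.
2. Have an existing team member who does none of that processing hold the key. Release it only after the cleaned data and the P2, N2 and P3b measurements are locked.
3. Amend the Randomization and blinding section to say that EEG processing is masked in this way, even if the later statistical modelling is not.
4. Reword the instructor statement to say what they are blind to: the cognitive component (CI or CC), the hypotheses, or both. It should not imply blindness to the exercise component.

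The cost is a recoding step, a key-holder, a short delay before labels are opened, and a few rewritten sentences. Coded IDs and separately filed linking lists already exist, which makes this look feasible, although the documents do not describe the team's capacity.
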